## Methods/Design

### Study Design

The study, called CHOICE, is a non-randomized, controlled trial in post-menopausal breast cancer survivors investigating whether an energy restricted dietary pattern, i.e. low carbohydrate, high fat or low fat, high carbohydrate, with progressive fat loss during a weight loss program can alter the likelihood of long term survival following treatment for breast cancer as reflected in metabolic and hormonal prognostic biomarkers. A total of 370 women will be accrued and assigned to one of the two dietary intervention arms based on eating preferences or a non-intervention control arm (n = 135 to each intervention arm, n = 100 to the control arm) and followed for 6 months as illustrated in Figure 1. Anthropometric measurements are conducted and biomarkers collected at baseline and 6 months in the control arm, and monthly in the intervention arms in order to model the shape of the metabolic and hormonal response curves.

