### Data Analysis

All data elements collected will be examined using descriptive statistics (mean, median, SD, range, percentiles, proportion) and graphical summaries (box plots, profile plots by time and diet group). Log transformations will be made before further analysis to stabilize variances as needed.

The primary hypothesis on C-reactive protein will be tested using the following ANCOVA model:

Where Y_4 _is the outcome measure at the end of 6 months, Y_1 _is the outcome measure at baseline, and, GLYC is a 2-level indicator for dietary pattern. This method of analysis adjusts for any remaining pre-treatment differences between groups (a precaution against imbalance after diet assignment) and reduces variability in the data being analyzed [97], thus improving the power of the test for the main effect of interest, b_2_.

There will be a wealth of information in the repeated measures on each subject; the results for all measures using all available data from all time points will be estimated in a mixed-effects repeated measures model to assess the slopes and between group differences after each month of weight loss [98]. The power of this approach lies in its ability to incorporate all of the available longitudinal data even in the unbalanced case, that is, when some of the observations are missing for one or more individuals. Observations within a person over time are allowed to be correlated while observations across individuals are assumed to be independent. These models will also be used to explore the effects of breast cancer stage, BMI (a time-varying covariate) and age.

Depending on the appearance of change over time (seen in the profile plots of each outcome measure by time and diet) linear or nonlinear mixed models will be used. If the trend appears to be linear, the following model for the response vector ***y***_i _for the *i*th group will be used:(1)

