Missing data are expected to be missing at random, and are unlikely to exceed 5% of all observations. This assumption will be checked during the initial descriptive analysis of the data after database lock, and appropriate sensitivity analyses will be done if there is evidence that the data are MNAR (missing not-at-random) [99]. Given the nature of the patient population and the incentives to return for monthly evaluations, we expect to collect most endpoint measures regardless of compliance. We will accrue 370 subjects with the expectation of completing at least 135 per diet group and 100 in the control group, that is, 10% loss to follow-up. Analysis will be intent-to-treat. All statistical analysis will be done using SAS version 9 (SAS Institute, Cary, NC).

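### Missing-data sensitivity analyses wait for evidence that observed data cannot give, and the primary month-6 ANCOVA, as written, leaves the monthly CRP of dropouts unused

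*Protocol article*

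**What the plan says.** All of the following is in the protocol article, in Data Analysis unless noted.

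- **Assumption:** "Missing data are expected to be missing at random, and are unlikely to exceed 5% of all observations".
- **Check:** "This assumption will be checked during the initial descriptive analysis of the data after database lock". The check is thus descriptive and made on the recorded data.
- **Trigger:** what follows depends on the outcome of that check: "appropriate sensitivity analyses will be done if there is evidence that the data are MNAR (missing not-at-random").
- **Primary CRP test:** an ANCOVA whose response "is the outcome measure at the end of 6 months, Y_1 _is the outcome measure at baseline, and, GLYC is a 2-level indicator for dietary" …, the two levels being the two diets. No rule for a missing month-6 value is given. The section also states: "Analysis will be intent-to-treat".
- **Other CRP analysis:** a repeated-measures mixed model on all time points is planned for all measures. Of it the article says: "The power of this approach lies in its ability to incorporate all of the available longitudinal data even in the unbalanced case". For the secondary measures, said to use the same methods as the primary, the mixed-model step is called exploratory and follows the ANCOVA.
- **Loss to follow-up:** 370 are accrued "with the expectation of completing at least 135 per diet group and 100 in the control group, that is, 10% loss to follow-up". Study Design gives the same figures as the numbers assigned: "n = 135 to each intervention arm, n = 100 to the control arm".
- **Data collected:** Study Design has biomarkers measured monthly in the diet arms and only at baseline and 6 months in the control arm. Eligibility gives seven blood samples per diet participant.

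**The concern.** There are two linked problems.

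**The trigger.** MNAR means that missingness depends on the unseen values even after conditioning on what was seen. A descriptive check can show that dropouts differ from completers on recorded data, which speaks against data missing completely at random. It cannot show whether the unrecorded month-6 values differ beyond what the recorded ones predict. The plan therefore makes its only protection against departures from MAR depend on evidence that its own check cannot produce. Because the check comes after lock, any decision to run or skip the analysis is taken with the data in hand.

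**The primary test.** MAR over the full series lets dropout depend on interim monthly results. An ANCOVA on women with an observed month-6 value is valid under a narrower condition: that dropout depends only on diet and baseline CRP. The primary test is thus weaker than the assumption the plan makes for it, although the data that would close the gap are collected in exactly the two arms being compared.

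The article recognises the risk. Its Dietary Adherence section says attrition in lifestyle studies can cause selection bias and overstate effects. Diets are assigned by eating preference and are not blinded (Study Design, Limitations), so dropout for different reasons in the two diets is plausible.

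**Working it through.** **1. The plan's own retention figure.** 135 + 135 + 100 = 370 completing out of 370 accrued is 0% loss, so the stated 10% is not reproduced. At 10% loss, 370 × 0.90 = 333 would complete: 121.5 per diet arm and 90 controls. For 135, 135 and 100 to complete, 135/0.9 = 150, 135/0.9 = 150 and 100/0.9 = 111.1 (112) would be needed, 412 in all. The 10% is used below as the article's own figure, subject to that contradiction. It means about 27 of 270 diet participants without month-6 CRP, and 243 in the ANCOVA.

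**2. 5% against 10%.** With seven visits, if 10% leave evenly after visits 1 to 6, the share of missing observations is 0.10 × mean(6, 5, 4, 3, 2, 1)/7 = 0.10 × 3.5/7 = 5.0%. The range is 0.10 × 1/7 = 1.4% (all miss only the last visit) to 0.10 × 6/7 = 8.6% (all leave after baseline). The two figures can both be true, but the primary endpoint is then 10% missing, not 5%.

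**3. Bias of the completer ANCOVA under MAR.** The article gives no SD or correlations, so these are assumptions: SD = 1 on the analysed scale, correlation 0.6 between baseline and each later value, and 0.8 between the interim and month-6 values. There is no true diet effect. In one diet, half of the women in the top 20% of interim CRP leave (10% in all); in the other, 10% leave at random.

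- Mean interim CRP of those who leave in the first diet: 0.280/0.20 = 1.40 SD, where 0.280 is the normal density at 0.842.
- Mean among those who stay: −(0.10/0.90) × 1.40 = −0.156.
- Shift at month 6 not removed by baseline adjustment: −0.156 × (0.8 − 0.6 × 0.6) = −0.156 × 0.44 = −0.068 SD.

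A simulation of 1,000,000 records under these assumptions gave −0.067 SD for the completer ANCOVA and +0.003 SD when missing values were predicted from baseline and interim CRP within diet. With the same selective mechanism in both diets, both methods gave about −0.001.

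Milder selection scales the figure down. If leavers average 0.65 SD above the mean, the bias is 0.111 × 0.65 × 0.44 = 0.032 SD. A separate simulation (135 per arm, about 10% dropout, driven by month-3 CRP in one arm, 3,000 runs) gave −0.031 SD with 5.9% rejection under the null. The Monte Carlo standard error of that rate is √(0.059 × 0.941/3000) = 0.4 points, so the inflation there is slight.

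**4. Departure from MAR.** If the 10% missing in one diet differ from prediction by k SD, the contrast moves by 0.10 × k: 0.025, 0.05 and 0.10 SD for k = 0.25, 0.5 and 1. The standard error with 121.5 per arm and baseline correlation 0.6 is √(1 − 0.36) × √(2/121.5) = 0.8 × 0.128 = 0.103 SD. A k of 0.5 therefore moves the contrast by about half a standard error, and nothing in the observed data can exclude it.

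**The case against.** Several points on the other side stand, and they limit what may be concluded.

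- **A reader might infer that the plan excludes women without a month-6 value and so contradicts its intent-to-treat statement.** The article never says so. Completer status follows from a model that needs the month-6 value, with no imputation mentioned. A full protocol or SAP, not shown, could supply a rule.
- **A reader might infer that no CRP analysis uses the partial data.** That is wrong. The mixed model on all available data is planned without condition and covers CRP. What is not guaranteed is an analysis under departures from MAR, and what is unprotected is the primary test.
- **A reader might infer that every dropout has monthly CRP.** It exists only up to dropout and only in the diet arms; a woman who leaves before the first monthly visit has baseline alone.
- **A reader might infer that the primary result will be biased.** Poor responders leaving alike in both diets produces a bias near zero. A difference in mechanism between diets is needed; it is plausible here but not shown. The article also expects to collect most endpoints regardless of compliance.

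None of this rescues the trigger. The article states that rule explicitly, so it is not a detail left to another document, and the rule cannot do what it is meant to do.

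**Conclusion.** The conditional trigger is wrong as stated, and this conclusion needs no assumed figures. The point about the primary test holds more narrowly. As written, the month-6 ANCOVA uses completers only and does not draw on the interim CRP that the plan's MAR assumption would let it use. The exposure is modest: about 0.03 to 0.07 SD if dropout depends on interim CRP in one diet but not the other, and about zero if the mechanism is shared. These figures rest on 10% dropout and on the assumed correlations. The 10% itself does not fit 370 accrued and 370 completing, so the number of women affected stays provisional until that is settled. This should be changed; it does not invalidate the design.

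**What to change.** 1. Replace the conditional clause with a pre-specified, unconditional delta-adjusted (tipping-point) sensitivity analysis of the month-6 diet contrast in CRP. Shift the missing month-6 values separately by diet over a stated range, and report where the conclusion changes.
2. Base the primary month-6 contrast on all monthly CRP values, with the completer ANCOVA as supportive. Either of two routes will do:
   - a repeated-measures model with categorical month, diet-by-month, baseline CRP and unstructured covariance; or
   - multiple imputation from the monthly values under the existing ANCOVA.

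   The first is a re-specification. The mixed model in the article has its form chosen after viewing profile plots and indexes assessments by 1.5 kg of fat loss, so it cannot simply be relabelled as primary.
3. Reconcile the 10% loss to follow-up with 370 accrued and 135 + 135 + 100 = 370 completing. Then state the expected missingness at month 6 separately from the 5% of all observations.

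The cost is a change of wording and modest extra analysis work. No new data are needed.

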### Intervention

Intervention participants follow a fully defined diet-physical activity program designed to create a weekly negative energy balance equivalent to 3500 kcal, after adjustments for metabolic adaptations that occur during extended periods of weight loss. The intervention groups (135 participants in each arm) receive the same physical activity protocol promoting published physical activity guidelines and translated into step recommendations [67,68], but one of two dietary patterns: low fat or low carbohydrate.

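### The accrual target (370), the completer targets (135 + 135 + 100 = 370) and the stated 10% loss to follow-up cannot all be right

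*Protocol article*

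**What the plan says.** Three parts of the protocol article give sample-size figures by arm.

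- **Data Analysis**, final paragraph: 370 women are to be accrued, and the plan counts on "completing at least 135 per diet group and 100 in the control group, that is, 10% loss to follow-up". Here 135/135/100 are minimum numbers of completers.
- **Study Design**: "A total of 370 women will be accrued and assigned to one of the two dietary intervention arms based on eating preferences" or to the control arm, with "n = 135 to each intervention arm, n = 100 to the control arm) and followed for 6 months". Here 135/135/100 are numbers assigned at the start.
- **Intervention**: "The intervention groups (135 participants in each arm) receive the same physical activity protocol". This again describes the arms as they begin the programme.

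The Methods/Design part of the abstract gives approximately 370 accrued. No section gives a larger enrolment, a replacement rule for women who leave, or a separate inflated number per arm.

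The primary test on C-reactive protein, also in Data Analysis, is an ANCOVA of the 6-month value on the baseline value and a two-level indicator for dietary pattern.

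**The concern.** The same three numbers serve as women assigned and as women who finish, while the text says that one in ten will be lost. A reader cannot tell how many women per diet arm the primary comparison is meant to have.

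The primary ANCOVA needs a 6-month value, and the article describes no imputation for it. The number completing is therefore close to the number that informs the main result. If the study was sized on 135 completers per diet arm, the planned accrual falls short of that at the stated loss rate. If it was sized on fewer completers and 135 is the enrolment number, only the label in Data Analysis is wrong.

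**Working it through.** **Inputs, all from the article**

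- Accrual: 370 (Study Design; Data Analysis)
- Completer targets: at least 135, 135 and 100 (Data Analysis)
- Numbers assigned: 135, 135 and 100 (Study Design)
- Loss to follow-up, d: 10% (Data Analysis)

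**Step 1. Try to reproduce the stated accrual.**
Sum of completer targets: 2 × 135 + 100 = 370.
Implied loss: 1 − 370/370 = 0%.
The accrual of 370 is reproduced only at zero loss, not at the stated 10%.

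**Step 2. Keep the completer targets and the 10%; solve for accrual.**
Formula: n / (1 − d), rounded up.
- Diet arm: 135 / 0.9 = 150
- Control arm: 100 / 0.9 = 111.1, so 112
- Total: 150 + 150 + 112 = 412, which is 42 more than planned

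The cruder n × (1 + d) does not give 370 either: 135 × 1.1 = 148.5, so 149; 100 × 1.1 = 110; total 149 + 149 + 110 = 408.

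**Step 3. Keep the accrual and the 10%; solve for completers.**
Formula: n × (1 − d), with the same loss in each arm.
- Diet arm: 135 × 0.9 = 121.5
- Control arm: 100 × 0.9 = 90
- Total: 370 × 0.9 = 333, which is 37 below the stated targets

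**Step 4. Effect on precision.**
The standard error of the diet comparison scales with 1/√n, so going from 135 to 121.5 per arm multiplies it by √(135/121.5) = √(1/0.9) = 1.054, an increase of 5.4%.

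**Step 5. Effect on power (illustration only).**
The article gives no significance level, power, effect size or standard deviation. Assume a two-sided 5% test that was sized on 135 per diet arm.
- If sized for 80%: Φ((1.960 + 0.842) × √0.9 − 1.960) = Φ(0.698) = 0.757, about 76%
- If sized for 90%: Φ((1.960 + 1.282) × √0.9 − 1.960) = Φ(1.115) = 0.868, about 87%
- Difference detectable with 80% power, in residual standard deviations: (1.960 + 0.842) × √(2/135) = 0.341 on 135 per arm, and 0.341 × 1.054 = 0.359 on 121.5 per arm

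The control arm does not enter this calculation, because the primary model compares the two dietary patterns.

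**The case against.** **Loss may already have been allowed for.** If 135/135/100 are enrolment numbers, inflated from about 121/121/90, then the only mistake is calling them completers, and any power calculation behind them is unaffected. This is a fair reading, and the text cannot rule it out. A reader might infer that the 10% loss was simply forgotten; the article does not establish that. What stands under either reading is that the sentence in Data Analysis is wrong as written.

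**Rounding or approximate wording.** The abstract says approximately 370, but the gap from 370 to 412 is about 11% (42/370 = 0.114), which that word does not cover.

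**Missing data are said to be "unlikely to exceed 5% of all observations".** A reader might take this as a second contradiction with the 10%, or as a sign that the true loss is smaller. Neither follows. The 5% counts observations and the 10% counts participants, and they can agree. If drop-out is spread evenly over months 1 to 6, a woman who leaves misses on average (6 + 5 + 4 + 3 + 2 + 1)/6 = 3.5 of 7 visits, so 10% drop-out gives 10% × 3.5/7 = 5% of observations. In the control arm, with two visits, 10% missing at month 6 is also 5%. The 5% statement is not an error. Nor would it rescue the completer targets if read as participant loss: 135/0.95 = 142.1, so 143; 100/0.95 = 105.3, so 106; total 143 + 143 + 106 = 392, still above 370.

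**Intent-to-treat analysis and mixed models.** These soften the loss for the longitudinal analyses, which use every available visit. They do not supply a 6-month value for the primary ANCOVA, and they do not change the arithmetic. The article also expects to collect most endpoint measures whatever a woman's compliance, but that concerns women who still attend, and most is not all.

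**The consequence is modest and conditional.** This is correct. The illustrated loss is 3 to 4 percentage points of power, and it arises only if 135 completers were the design number.

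**Conclusion.** The contradiction is certain and rests only on the article's own figures: 370 completers out of 370 accrued is no loss at all, yet 10% is stated. The size of the discrepancy is 37 completers too many for an accrual of 370, or 42 women too few for the stated completer targets.

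The figure of about 121 per diet arm holds only if 370 is the true accrual and the loss is 10% in each arm. The article does not support a claim that the trial is underpowered: it states no power, so the fall from 80% to about 76%, or from 90% to about 87%, is an illustration that assumes a two-sided 5% test sized on 135 per arm. The article also does not show which of the three figures is mistaken. The primary outcome and the primary model are untouched.

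**What to change.** Reconcile accrual, completers and loss rate so that the three agree wherever they appear (abstract, Study Design, Intervention, Data Analysis), and state which number the sample size rests on.

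- **If accrual stays at 370:** reword the sentence in Data Analysis along these lines: *Accrual is 370 (135 in each diet arm and 100 controls); allowing for 10% loss, about 121 women per diet arm and 90 controls are expected to complete.* State any power or detectable difference for the primary 6-month ANCOVA on about 121 per diet arm. This costs wording only and needs no extra participants. The stated figure becomes slightly less favourable and, if 135 completers per arm were the design number, the shortfall is openly accepted.
- **If 135/135/100 completers are required:** restate accrual as about 150/150/112, 412 in total, in every section that now gives 370 or 135 per arm. This costs 42 more women.

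The choice belongs to the investigators, who know how the 135 was derived. The statement about missing observations needs no change.

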### Limitations

Limitations include the fact that the study is neither double blinded nor randomized; results may not be generalizable. The population is free living and as such is subject to issues of compliance and difficulties with quantifying dietary intake and physical activity.

## Discussion

A number of reports indicate that the prognosis for long term survival following treatment for breast cancer is better in women whose body weight for height, assessed by body mass index (BMI, body weight (kg)/height (m^2^)), is considered to be in the normal range (BMI 18.5 to 24.9) versus women who are overweight (BMI 25.0 to 29.9) or obese BMI ≥ 30.0 [1,4,6,7,9-13,100,101]. Consistent with those reports is the observation that weight gain post diagnosis increases risk for breast cancer recurrence; whereas, weight loss in breast cancer survivors improves the chances of long term survival [20,21]. If one takes the available epidemiological and clinical data at face value, it prompts the question of why relatively little attention is paid to weight control in the clinical management of breast cancer survivors post treatment.

Overweight and obesity are common problems in the United States, and there is little evidence to indicate that prevalence is less in breast cancer survivors than in the population at large, which is estimated to be > 60% [17]. Obesity has been reported to be the cause for at least 9% breast cancer cases [102]. Thus, given that the majority of breast cancer survivors have excess weight as a risk factor, the population at risk is large. However, a number of challenges are faced by the physician. They include issues such as initiating a conversation about weight loss while recognizing the sensitivity of the subject and time constraints of office visits, which do not allow sufficient time to address the complexity of individual weight management issues, including the knowledge and behavioral gaps related to diet and weight loss. Moreover, there may be hesitation to emphasize weight loss given the recognized 95% long term failure rates of most weight control efforts, making this information a lower priority during the office visit [22,103-110]. Additionally, due to lack of knowledge about the subject matter, basic questions such as, 'How should weight loss be achieved?' and, 'How much weight loss will provide benefit?' cannot be answered with confidence. While many studies have examined differences in effectiveness among various approaches to weight loss [22,103-110], relatively few studies have been conducted in a free living population of breast cancer survivors in the private practice setting. This study will provide information that can be used to answer patient's questions about the effects of dietary pattern and magnitude of weight loss on long term survival following breast cancer treatment.

